## 4. STUDY POPULATION

### 4.1 Population (base)

Patients ( $\geq 18$  years) who are diagnosed with gastric adenocarcinoma are eligible to participate in the study. The centres perform 20-30 gastric resections per year. A total number of 210 patients is required for inclusion, which makes the inclusion time of 3 years feasible.

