### 4.4 Sample size calculation

The primary outcome parameter is postoperative hospital stay. A recent meta-analysis has shown that laparoscopic procedure shortens the median hospital stay with 4 days (12).

Hospital stay after laparoscopic gastrectomy: 14 days

Hospital stay after open gastrectomy: 18 days

Significance level ( $\alpha$ ) = 0.05

Power ( $1-\beta$ ) = 0.80

Sample size:

Total number of 210 participants:

- Laparoscopic gastrectomy (experimental arm) = 105
- Open gastrectomy (conventional surgery) = 105

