## 5. TREATMENT OF SUBJECTS

The investigational surgery is the laparoscopic gastrectomy (distal and total). The conventional surgery treatment consists of conventional open gastrectomy (distal and total). Both techniques are described underneath.

Patients will receive a distal gastrectomy or total gastrectomy, depending on tumor location on preoperative diagnostics (Endoscopic ultrasonography [EUS], gastroscopy and CT-scan). For tumors located in the antrum a distal gastrectomy will be performed, whereas for tumors located in the corpus, and diffuse gastric cancer, a total gastrectomy will be performed (13).

Basic summary of the surgical procedure:

- Distal gastrectomy with D2 lymph node dissection (figure 3)
- Total gastrectomy with D2 lymph node dissection (figure 3)

Several types of reconstruction types can be performed (i.e. jejunal pouch or no pouch), according to the preference of the surgeon. Also the type of anastomosis (i.e. end-to-end, end-to-side or side-to-side) either stapled or hand sewn may be performed according to the individual surgeon's insight.

| Distal gastrectomy                                                                                                                | Total gastrectomy                                                                        |
|-----------------------------------------------------------------------------------------------------------------------------------|------------------------------------------------------------------------------------------|
| D1: Station 1,3,4sb, 4d, 5, 6, 7
D1+: Station 1,3,4sb, 4d, 5, 6, 7, 8a, 9
D2: Station 1,3,4sb, 4d, 5, 6, 7, 8a, 9, 11p, 12a | D1: Station 1-7
D1+: Station 1-7, 8a, 9, 11p
D2: Station 1-7, 8a, 9, 11p, 11d, 12a |
| [figure not shown]                                               | [figure not shown]     |

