#### Postoperative policy

To ensure fast recovery, the ERAS protocol is followed. A consensus meeting between the participating centers is organized to discuss the pre- and postoperative protocol (17).

- Epidural analgesia will be given following open gastrectomy only. Other analgesia can be given without limitations to reach adequate pain control.
- Urinary catheterization can be done when indicated.
- Enteral feeding via a jejunostomy catheter can be given to patients who underwent total gastrectomy, according to the local hospital's policy. No jejunostomy catheter will be placed following distal gastrectomy.
- At postoperative day 1, patients will be encouraged to start liquid oral feeding.
- Mobilization under supervision of a physiotherapist starts as soon the patient is stable.
- Nasojejunal tubes for decompression will not be used (17).

However, the treating physician may implement a deviation from the protocol to avoid causing any harm or if there is a safety hazard to trial subjects without prior approval from the ethics committee.

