## **6.2 Randomisation, blinding and treatment allocation**

After completion of preoperative chemotherapy and signing informed consent at the outpatient clinic, participants will be randomized by means of an online random number generator, stratified by centre. Randomization will be performed by the coordinating investigator and directly provided to the participating centres. The data-analyst will be blinded for the procedure.

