### 8.1 Primary study parameter

The primary outcome measure is postoperative hospital stay. This variable is expected to have a non-Gaussian distribution and will therefore be analysed by means of a Mann-Whitney-U test in univariate analysis.

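### Randomisation is stratified by centre but the fixed primary test ignores centre: the test stays valid, but may be conservative and slightly inefficient

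*Protocol*

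**What the plan says.** - **Allocation.** Section 6.2 states that "participants will be randomized by means of an online random number generator, stratified by centre". It mentions no blocks, block size or minimisation.
- **Primary test.** Section 8.1 expects hospital stay to be non-Gaussian and says that it "will therefore be analysed by means of a Mann-Whitney-U test in univariate analysis". Section 8 adds only intention to treat, and chi-square or Mann-Whitney tests for the other outcomes. Centre appears in none of these analyses.
- **Care that may differ by centre.** Under Postoperative policy in section 5: "Enteral feeding via a jejunostomy catheter can be given to patients who underwent total gastrectomy, according to the local hospital's policy". The Total gastrectomy text in section 5 also leaves the jejunal pouch and feeding jejunostomy to each hospital, and the opening of section 5 leaves reconstruction and anastomosis to the surgeon.
- **Type of resection.** Section 5: "Patients will receive a distal gastrectomy or total gastrectomy, depending on tumor location on preoperative diagnostics". It is known before surgery but is not a stratification factor.
- **Number of centres.** Not stated. Section 4.1 says only: "The centres perform 20-30 gastric resections per year".

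**The concern.** When allocation is forced to balance within centres, differences between centres largely cancel out of the comparison of arms. A pooled rank test still counts those differences in its variance. Its standard error is then too large, its P values tend to be too large, and some of the precision bought by stratifying is lost.

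The protocol does not leave this open: it names the test and calls it univariate, so an SAP that put centre into the primary test would depart from section 8.1. At stake are a few points of power in a trial planned at 80% with no stated margin. The risk of a false positive claim is not increased.

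**Working it through.** **Inputs from the protocol.** Section 4.4: "Hospital stay after laparoscopic gastrectomy: 14 days" and "Hospital stay after open gastrectomy: 18 days", alpha 0.05, power 0.80, 105 per arm. Two-sided testing is assumed.

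**Inputs that had to be assumed.**
- Spread of stay: none is stated, so it is solved for below.
- Centre share of variance: 0 to 0.20.
- Centres: 5, 10 or 15 of equal size, that is 42, 21 or 14 patients each. Over the 3-year inclusion period this is 14, 7 or about 5 patients per centre per year, all below the 20-30 resections per year in section 4.1.

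**Step 1: the plan's own figure.** The total of 210 cannot be checked without an SD, but the SD that it implies can be found. With n per arm = 2(1.96 + 0.8416)² SD² / 4², setting n = 105 gives SD ≈ 10.35 days. For the rank test, Noether's formula gives 210 = (1.96 + 0.8416)² / [12 × 0.25 × (p − 0.5)²], so p ≈ 0.61. For lognormal stay with medians 18 and 14, p = Φ(ln(18/14) / (σ√2)), so σ ≈ 0.627 on the log scale. This is the base case with 80% power.

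**Step 2: approximation for exact balance within centre.** If a share ρ of the rank variance lies between centres, the true variance of the rank statistic is (1 − ρ) times the one the unstratified test uses.
- Size, unstratified: 2[1 − Φ(1.96/√(1 − ρ))]
- Power, unstratified: Φ(0.8416/√(1 − ρ))
- Power, stratified: Φ(2.8016/√(1 − ρ) − 1.96)

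| ρ | Size, unstratified | Power, unstratified | Power, stratified |
|---|---|---|---|
| 0.05 | 0.044 | 0.806 | 0.820 |
| 0.10 | 0.039 | 0.813 | 0.840 |
| 0.20 | 0.028 | 0.827 | 0.879 |

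**Step 3: simulation.** 20,000 trials per cell, stay rounded to whole days, unstratified Mann-Whitney against van Elteren by centre. The Monte Carlo standard error is about √(0.05 × 0.95/20,000) = 0.0015 for size and √(0.8 × 0.2/20,000) = 0.003 for power. Ranges run over 5, 10 and 15 centres.

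*Blocks of 4 within centre*

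| Centre share | Size, unstratified | Size, stratified | Power, unstratified | Power, stratified | Change in points (5 / 10 / 15 centres) |
|---|---|---|---|---|---|
| 0 | 0.047-0.052 | 0.049-0.051 | 0.81 | 0.78-0.80 | −0.6 / −1.6 / −2.5 |
| 0.05 | 0.045-0.047 | 0.048-0.051 | 0.81 | 0.80-0.82 | +0.6 / −0.3 / −1.3 |
| 0.10 | 0.041-0.043 | 0.050-0.052 | 0.82 | 0.82-0.84 | +1.9 / +1.3 / −0.3 |
| 0.20 | 0.031-0.034 | 0.048-0.050 | 0.83-0.84 | 0.86-0.88 | +4.0 / +3.7 / +3.3 |

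The sizes are less extreme than in step 2. A likely reason is that balance is not exact: 42, 21 and 14 are not multiples of 4.

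*Simple randomisation within centre.* The unstratified test has size 0.048-0.052 at every centre share, because chance imbalance within centres brings the between-centre variance back into the comparison. The change in power from stratifying, for 5 / 10 / 15 centres, is −1.4 / −3.6 / −5.4 points at share 0, +0.2 / −1.3 / −3.3 at 0.05, +1.8 / +0.8 / −1.2 at 0.10 and +5.2 / +4.6 / +2.8 at 0.20.

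**Step 4: gastrectomy type.** The protocol gives no difference in stay between distal and total resection, and its meta-analysis figure for stay is for total gastrectomy. No size is claimed for adjusting for type.

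**The case against.** The case for leaving the test alone is substantial.

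- **Validity.** A reader might infer that the P value is wrong. The documents do not support that. Any error is conservative, and it needs both balanced allocation within centre and a real centre effect. Stratifying does little unless allocation is restricted within strata, so blocks are a natural reading of section 6.2, but the section does not say so. This part of the objection stands.
- **Centre differences.** A reader might take variation by centre or by type of resection as known. The protocol gives no figure for either. Some of its text points towards uniform care: an ERAS protocol and a consensus meeting between centres (Postoperative policy), common criteria attached to the endpoint (6.1.1), and shared training, completed learning curves and proctoring (Surgical Quality Control). Centre differences are plausible from the local-policy sentences, but no more than that.
- **Benefit.** The gain is small and reverses with many small centres and a centre share of 5% or less. This stands and is part of the verdict.
- **Gastrectomy type.** A reader might see its omission as a bias. It is not a stratification factor, so leaving it out costs efficiency only.
- **Effect estimate.** Section 8.1 names no estimate in days with a confidence interval. An SAP commonly supplies this, so it is not counted here.

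What survives is that the protocol fixes a primary test that ignores its only stratification factor.

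**Conclusion.** The mismatch between sections 6.2 and 8.1 is real and its consequence is modest. The Mann-Whitney test remains valid. Under blocks of 4 and a centre share of 10-20%, its true size is about 0.031-0.043, and a centre-stratified test gains about 0-5 points of power: roughly −0.3 to +4 in simulation, and 3 to 5 under the exact-balance approximation. At a share of 5% or less with 10-15 centres, stratifying brings no gain and can cost up to about 1-3 points, or about 5 with simple randomisation. With simple randomisation within centre there is no conservatism to correct.

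These figures assume two-sided testing, equal centres, lognormal stay and a log-SD back-solved from the planned power. Neither the number of centres nor the centre effect is in the protocol. Label: cheap improvement.

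**What to change.** In section 8.1, before any results by arm are seen, replace the unstratified test with one that accounts for centre. Two candidates are the van Elteren (centre-stratified Wilcoxon) test and a proportional-odds model with centre. Only the former was simulated here. Add a prespecified rule for pooling small centres, which limits the loss of power when centres are many and small. State in section 6.2 whether allocation is blocked within centre, since this decides whether the unstratified test is conservative at all.

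Planned distal or total gastrectomy may be added as a covariate in a prespecified supportive model, for efficiency only. It should be the type planned before surgery. Section 6.1.3 does not list it as a baseline variable, so it should be recorded explicitly or derived from the preoperative work-up.

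The cost is protocol wording, a pooling rule and the possible small loss of power described above. Centre is known for every patient, and the sample size need not change.

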### 8.2 Secondary study parameters

Binary variables will be displayed in cross-tabulations. The Person  $\chi^2$  will be used for analysis between groups.

Variables with a non-Gaussian distribution and will be analysed by means of a Mann-Whitney-U test in univariate analysis.

Statistical significance is defined as  $P < 0.05$ .

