**Nature and extent of the burden and risks associated with participation, benefit and group relatedness:**

Patients will undergo either laparoscopic gastrectomy (experimental arm) or the conventional open gastrectomy (conventional surgery). Tumor biopsies will be collected pre-operatively. Blood samples will be drawn at baseline, direct postoperatively and on postoperative day 2. Patients are required to fill out quality of life questionnaires (preoperatively and  $<5$  days, 6 weeks, 6 months, and yearly up to 5 years postoperatively). Laparoscopic gastrectomy was demonstrated to be safe in our own series of 30 patients treated in the UMC Utrecht as well as in our recent meta-analysis of the literature.

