### **6.1.2 Secondary study parameters/endpoints**

- Oncologic outcome:
  - Resection margins in millimeters
  - R0 resection (complete resection with no microscopic residual tumor)
  - Number of lymph nodes dissected
  - Number of tumor positive lymph nodes dissected
- Postoperative morbidity and mortality (19) (see appendix 1)
- Quality of Life: EQ-5D-5L, EORTC QLQ-30, EORTC QLQ-STO22 (see appendix 2)
- Cost-effectiveness: (see appendix 3)
  - SF-HLQ
  - Health care use
  - Costs of the procedure, hospital stay and re-interventions
  - Post-operative quality of life and productivity
- Readmission

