### **6.1.3 Other study parameters**

Baseline characteristics:

- Gender
- Age
- ASA-classification
- Body Mass Index
- Comorbidities
- Sarcopenia (see appendix 8)
- Intoxications
- Perioperative chemotherapy

Postoperative outcomes:

- Operation characteristics:
  - Duration of surgery
  - Blood loss during operation
  - Conversion to alternative surgical procedure

- Postoperative course:
  - Duration of Intensive Care stay
  - Duration of Medium Care stay
  - Mechanical ventilation
  - Vital signs (heart rate, blood pressure, temperature)
- Overall survival
- Disease free survival (absence of local or distant recurrence)
- Patients experience:
  - Pain: VAS-score (see appendix 4)
  - Time to return to daily activity (days)
  - Time to return to normal nutritional regime (days)
- Weight at day 5 after surgery or at discharge in case of discharge before day 5.
- Ergonomics surgeon: SMEQ questionnaire (see appendix 5)
- Learning curves of participating centers

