## **6.3 Study procedures**

Patient will undergo one of the following surgical procedures:

Laparoscopic gastrectomy: n= 105

Open gastrectomy: n= 105

Additional measures:

| Pre-operative                                                        | Post-operative                                                                                                                                                                                |
|----------------------------------------------------------------------|-----------------------------------------------------------------------------------------------------------------------------------------------------------------------------------------------|
| Blood sample for biobanking and baseline                             | Blood 6h postoperatively and on postoperative day 2.                                                                                                                                          |
|                                                                      | VAS-score for pain and vital signs during hospital stay                                                                                                                                       |
| QoL assessment
Groningen Frailty Indicator
Score
SNAQ score | QoL assessment and VAS scores for pain at 6 weeks, 3, 6, 9 months and 1-5 year after surgery.
Productivity assessment (SF-HLQ questionnaire)
Health care use (questionnaire appendix 3) |

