#### 6.6 Follow-up of subjects withdrawn from treatment

Patients who withdraw from the study will be followed-up until moment of withdrawal.

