### 8.3 Other study parameters

Binary variables will be displayed in cross-tabulations. The Person  $\chi^2$  will be used for analysis between groups.

Variables with a non-Gaussian distribution and will be analysed by means of a Mann-Whitney-U test in univariate analysis.

Statistical significance is defined as  $P < 0.05$ .

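### Sections 8.2 and 8.3 name only chi-square and univariate Mann-Whitney tests: neither handles patients who withdraw before 60 months in the survival analyses, and quality of life is compared without its preoperative score

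*Protocol*

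**What the plan says.** Protocol section 6.1.3 lists "Overall survival" and "Disease free survival (absence of local or distant recurrence") among the other study parameters. Section 8.3, which has the same title, gives their analysis. It opens with "Binary variables will be displayed in cross-tabulations", compares these by Pearson chi-square, sends non-Gaussian variables to a univariate Mann-Whitney test, and sets significance at P < 0.05. Follow-up is 60 months after surgery (Summary). For withdrawals, section 6.6 states: "Patients who withdraw from the study will be followed-up until moment of withdrawal".

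Section 6.1.2 makes quality of life a secondary endpoint ("Quality of Life: EQ-5D-5L, EORTC QLQ-30, EORTC QLQ-STO22 (see appendix 2"). It is measured before surgery and soon after it (Summary, burden paragraph: "Patients are required to fill out quality of life questionnaires (preoperatively and" within 5 days, and later). Section 6.3 then schedules "QoL assessment and VAS scores for pain at 6 weeks, 3, 6, 9 months and 1-5 year after surgery". The overview of activities in section 3 adds that a single quality-of-life questionnaire goes out at 3 and 9 months. Section 8.2 governs these data with the same two rules: "Variables with a non-Gaussian distribution and will be analysed by means of a Mann-Whitney-U test in univariate analysis".

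Section 8 names no time-to-event, covariate-adjusted or repeated-measures method.

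**The concern.** A patient who withdraws at, say, 20 months without having died has a survival time known only to exceed 20 months. Mann-Whitney must either treat 20 months as the time of death or drop the patient. A chi-square on five-year status must either count the patient as alive or exclude the patient, and exclusion sits badly with the intention-to-treat commitment in sections 3, 6.4 and 8. The two workarounds err in opposite directions: ranking makes the arm with more withdrawal look worse, and counting as alive makes it look better. If withdrawal differs between arms, either test can therefore signal a survival difference that does not exist. The trial is unblinded, so a difference is possible, although the protocol gives no sign of one.

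For quality of life, a two-sample test on one visit has no place for the preoperative score as a covariate and does not link a patient's visits. At stake there is precision. In addition, no main time point is named, so several scales over up to ten postoperative visits can each be tested at 0.05.

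**Working it through.** **Plan's own figure.** Sections 8.2 and 8.3 contain no calculated figure, so there is none to reproduce. The 210 patients in section 4.4 are sized for hospital stay only.

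**Survival: inputs.** From the protocol: 105 per arm (4.4); fixed 60-month follow-up (Summary; section 3); five-year survival of 45% after curative resection, with another 10% from perioperative chemotherapy (section 1), so 45-55%. Assumed, because the protocol gives no value: exponential survival, exponential withdrawal with the stated five-year probability, hazard ratio 0.70 where a difference exists, two-sided 0.05.

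**Step 1: patients alive at 60 months.** Expected number: 210 × 0.45 = 94.5 to 210 × 0.55 = 115.5. Every patient has the same 60-month limit, so survivors share one censoring time and can be ranked as ties at the top. The first and fifth rows below show that this does no harm to error rates.

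**Step 2: simulation with withdrawal.** 4000 trials per row, 45% five-year survival. The Monte Carlo standard error at 5% is √(0.05 × 0.95 / 4000) = 0.3 points.

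| True HR | Withdrawal by 5 years, by arm | Log-rank | Mann-Whitney on observed time | Chi-square, withdrawn counted alive |
|---|---|---|---|---|
| 1 | none | 4.9% | 4.8% | 4.6% |
| 1 | 10% / 10% | 5.0% | 5.4% | 4.8% |
| 1 | 5% / 15% | 5.2% | 9.8% | 6.2% |
| 1 | 5% / 25% | 4.9% | 26.6% | 10.5% |
| 0.70 | none | 44% | 43% | 40% |
| 0.70 | 10% / 10% | 42% | 36% | 38% |

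Rows with HR 1 show type I error; rows with HR 0.70 show power. Mann-Whitney on deaths only has 7% power in the last scenario. A repeat simulation gave about 11% and 30% for Mann-Whitney in the two unequal rows; over the runs with 10% withdrawal per arm, power was 32-36% for Mann-Whitney and 37-42% for log-rank. At 55% five-year survival, the 5% / 25% case gives 35% for Mann-Whitney, 9.7% for chi-square and 5.4% for log-rank.

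**Quality of life: inputs.** 105 per arm from section 4.4. Assumed: a difference of 0.35 SD, and a correlation ρ between baseline and follow-up of 0.3 to 0.7.

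**Step 3: precision.** Adjusting for baseline multiplies the variance by 1 − ρ². Power = Φ(0.35 / √(1 − ρ²) × √(105/2) − 1.96).

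- Unadjusted: 0.35 × 7.246 = 2.536; 2.536 − 1.96 = 0.576; power 72%.
- Unadjusted with the rank-test efficiency 3/π = 0.955, which applies to normal data: effective n = 100.3; 2.478 − 1.96 = 0.518; power 70%.
- ρ = 0.3: variance × 0.91; 2.536/√0.91 = 2.659; power 76%.
- ρ = 0.5: variance × 0.75; 2.536/√0.75 = 2.928; power 83%; equivalent to 105/0.75 = 140 per arm.
- ρ = 0.7: variance × 0.51; 2.536/√0.51 = 3.551; power 94%.

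Testing change scores would not recover this. Their variance is 2(1 − ρ) = 1.4, 1.0 and 0.6 times that of the raw score: worse than no adjustment at ρ = 0.3, equal to it at 0.5, and still above 0.51 at 0.7.

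**The case against.** **These are default rules, and an SAP may add to them.** Sections 8.2 and 8.3 sort by variable type, name no endpoint, and give no test for Gaussian variables, so they are not exhaustive. That is a fair reading. But 8.3 carries the title of the list that holds both survival endpoints and names only two tests. An SAP that used log-rank or Cox would be departing from the protocol's text, not filling a silence. If 8.3 is not meant to cover survival, it should say so.

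**A reader might infer that about half of the patients are lost because they are alive at 60 months.** The documents do not support this. Follow-up is the same fixed length for everyone, survivors are ties, and without withdrawal Mann-Whitney performs almost like log-rank. The 45-55% survival figure therefore does not measure harm.

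**A reader might also infer that survival results would necessarily be biased.** They would not. With equal withdrawal, type I error stays near 5%; clear inflation needs unequal withdrawal, for which the protocol gives no figure.

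**The quality-of-life half is a choice of method.** In large part this stands. Under randomisation the unadjusted comparison is unbiased, the protocol does not say whether raw or change scores are compared, and for skewed scores a rank test may be more efficient than a mean-based model. What remains is avoidable loss of precision on a secondary endpoint whose baseline is already collected.

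**Conclusion.** The point holds in a limited form. For overall and disease-free survival, the tests named in 8.3 do not handle patients who withdraw before 60 months. If withdrawal is equal, the loss is a few points of power (about 32-36% against 37-42% at an assumed hazard ratio of 0.70 and 10% withdrawal per arm). If it is unequal, at an assumed 5% vs 15% up to 5% vs 25%, type I error is about 10-30% for Mann-Whitney on observed time, somewhat higher if survival is 55%, and about 6-10% for chi-square. Log-rank stays near 5% throughout.

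For quality of life, the stated test is valid but gives up precision: variance could be multiplied by 0.91, 0.75 or 0.51 at an assumed correlation of 0.3, 0.5 or 0.7. This is not a bias, and the text does not say that baseline scores are thrown away.

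The correction should be made, but it is not critical. The survival endpoints are listed as other parameters, quality of life is secondary, and the primary analysis of hospital stay is unaffected.

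**What to change.** **Section 8.3:** state that overall and disease-free survival are analysed by Kaplan-Meier curves, a log-rank test stratified by centre (as the randomisation is), and a Cox hazard ratio with 95% confidence interval. Time runs from randomisation, and patients without an event are censored at last contact. Keep the two existing rules for the remaining parameters.

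**Section 8.2:** state that each quality-of-life scale is analysed with a mixed model for repeated measures containing baseline score, centre, visit, arm and arm-by-visit, using the visits at which that scale is collected. Name one main time point.

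**Cost:** protocol and SAP wording only; the schedule already collects the data and no patients are added. The downside is a little more analysis work and reliance on a mean-based model for scores that may be skewed; a rank test at the main time point could be kept as a sensitivity analysis.
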